### Exclusion criteria

(1) History of premorbid neurocognitive decline (e.g. dementia, stroke); (2) currently requiring antipsychotic treatment for psychotic illness; (3) current use of medications for agitation, including olanzapine, from which they are unable to be weaned; (4) pregnancy or lactation; (5) known allergy to olanzapine; (6) participation in another study involving an investigational product; (7) otherwise determined to be unfit for participation due to medical considerations.

### Recruitment

Patients admitted to the Epworth HealthCare ABI Unit are routinely screened for PTA status using the WPTAS on admission. Those deemed to be in PTA have the WPTAS and ABS completed on a daily basis by a clinical neuropsychologist or nurse until they emerge from PTA. Study staff will be alerted to potential participants by ABI ward staff. Potential participants include patients in PTA who are exhibiting clinically significant agitation or thought likely to become agitated (due to factors such as agitation during acute hospitalisation). Due to their confusion and inability to lay down new memories, patients in PTA are not cognitively capable of consent. Recruitment will therefore target the patient’s MTDM. This will follow a two-stage process. Firstly, the study will be introduced to the patient’s MTDM by a member of their treating medical team and verbal consent for contact from study staff will be gained. Rapid consent processes are important to recruitment given the time-limited nature of PTA. The decision to introduce the trial to MTDMs of those patients determined likely to become agitated (rather than only those presently agitated) has been made in an effort to expedite the recruitment process and avoid exclusion of eligible participants. Agitation levels of those patients not presently agitated are monitored by study staff. If consent for contact is obtained and the patient is agitated at any stage during PTA, study staff will then contact the MTDM to carry out study consent procedures.

Participant recruitment commenced in June 2019, with the aim of recruiting participants until June 2022. Given that the full study protocol will have a duration of approximately 3 months, on average, data collection will continue until the end of September 2022. Epworth HealthCare treats more than 110 new patients with TBI annually, of whom 80 are likely to be in PTA on admission. Recent research studying this population within the Epworth HealthCare ABI ward [26] showed that 42.4% of TBI patients exhibited significant agitation according to the ABS whilst in PTA. Therefore, approximately 34 patients in PTA are likely to exhibit clinically significant agitation annually. Allowing for declined consent and ineligibility, we envisage recruitment of our sample over a 41-month period.

Participants for whom consent is obtained and who are randomised but do not receive the study intervention (e.g. due to the expiration of agitation) will not be replaced. Participants for whom consent is obtained but who are not randomised will be replaced. Participants for whom consent is obtained and who are randomised, receive the study intervention and are subsequently withdrawn from participation will not be replaced. Participants and MTDMs will not be paid for their participation in the trial.

### Consent

#### Identifying an Advance Care Directive/Medical Treatment Decision Maker

Due to their confusion and inability to lay down new memories, it is not possible to obtain consent from patients in PTA. In such circumstances, Australian law stipulates that researchers must first identify the presence of an Advance Care Directive (ACD; a legal document describing the patient’s wishes regarding their medical care). If there is a relevant instructional directive refusing a medical procedure involved in the research project, dissent will be assumed. If there is no instructional directive relevant to one or more of the study’s procedures, consent to research must be made by the patient’s MTDM, the individual who has legal authority to make medical decisions about the patient. If no ACD or MTDM can be identified for a possible participant, that patient’s enrolment into the study will be sought from the Office of the Public Advocate, Victoria, Australia’s governing body who may make such decisions according to law. Identification of an ACD/MTDM will be documented.

#### MTDM consent

If no relevant instructional directive refusing a medical procedure involved in the trial exists and the patient’s MTDM verbally consents to contact, consent will be sought by study staff in-person or via telephone. The option of telephone consent from study staff is being used given the challenges of gaining in-person access to the MTDM in an inpatient hospital setting before the expiration of agitation and PTA. Telephone consent will be thoroughly documented and include detailed verbal explanation of the study and opportunity to have questions answered. If telephone consent is obtained, this will be followed by written consent in-person or via post. If telephone consent is obtained but signed consent is not returned via post, telephone consent and documented identification of that individual as the MTDM will be considered sufficient.

#### Participant consent

Participant consent will be sought by study staff following that participant’s emergence from PTA and having been declared cognitively capable of consent by their treating clinical neuropsychologist. Failure to meet either of these criteria will result in the consent of the MTDM being maintained. In such cases, study staff will continue to monitor whether participants meet criteria for consent for the duration of their admission to the Epworth HealthCare ABI ward.

#### General aspects

All written consent procedures will employ a Medical Treatment Decision Maker Participant Information and Consent Form or Participant Information and Continuing Consent Form, as appropriate. In-person consent will include verbal explanation of the study and the opportunity to have any questions answered. In all instances, two copies of the consent form will be signed by the consenting party and study staff. Each party will retain one copy.

Some physicians and clinical neuropsychologists involved in an individual’s treatment whilst at the Epworth HealthCare ABI Unit are investigators on this study. In an attempt to mitigate any influence this dual relationship may have on the decision of a patient or MTDM to participate in this research, consent procedures will be carried out by a study staff member who is not a part of the patient’s treating medical team. Further, patients and MTDM will be assured that refusal to participate will not impact upon the standard of treatment offered by Epworth HealthCare.

Every effort will be made to enrol participants from non-English speaking backgrounds into the study, provided sufficient communication can be established in order for consent to be obtained, and study procedures are both understood and able to be completed. In the case of reading or writing difficulties, study staff may read the consent form aloud and/or obtain verbal consent in the presence of a witness. Both the witness and researcher obtaining verbal consent will sign and date the applicable consent form to document consent.

Participants and MTDMs may withdraw consent at any time. Should consent be withdrawn, permission will be sought to use data collected up until the point of withdrawal, and for the continued collection of data that does not require active participation by the participant (that is, measures that the hospital would undertake regardless of study participation). The participant’s or MTDM’s wishes regarding this matter will be reflected on the Form for Withdrawal of Participation, found at the end of the appropriate consent form.

This trial is not affiliated with any ancillary studies. Hence, consent to such research will not be sought.

### Screening

Study staff will be alerted to potential participants (in PTA according to the WPTAS and exhibiting or thought likely to exhibit agitation) by Epworth HealthCare ABI ward staff. Following consent procedures, a member of study staff or ABI unit medical registrar will screen this patient for study eligibility. Following confirmation of eligibility, the participant will be allocated the next available sequential participant number.

Some patients may already be taking medications for agitation, such as olanzapine, at this time. If they are deemed by study psychiatrists and the participant’s treating physician as able to be weaned off these medications, this will be done. Commencement of the study product may be carried out as participants are weaned off existing agitation medication, should this be deemed safe by study psychiatrists and the participant’s treating physician. In regard to current olanzapine use, commencement of study product may be initiated the following evening providing a dosage of no more than 10 mg per day has been administered in the last 24 h.

### Intervention, randomisation and allocation

Treatment will be administered by ward staff orally in capsule form. Study product may also be administered via nasogastric or percutaneous endoscopic gastrostomy (PEG) tube. Each active capsule will contain 5 mg olanzapine and 137.5 mg Flocel (filler). Placebo capsules will contain 142.5 mg Flocel (filler). Dosage will be flexible and titrated as follows: (1) one capsule at night (5 mg olanzapine or matching placebo per day); (2) one capsule in the morning, one capsule at night (10 mg olanzapine or matching placebo per day); (3) one capsule in the morning, two capsules at night (15 mg olanzapine or matching placebo per day); and (4) two capsules in the morning, two capsules at night (20 mg olanzapine or matching placebo per day). Dosage may be escalated every 3 to 4 days. The decision to escalate dose will be made based on whether ABS score reduces between dose escalation days, the clinical appropriateness of dose escalation and whether that participant’s ABS score is in the agitated range (ABS > 21). Should a participant’s ABS score fall below the agitated range (ABS < 22) whilst in PTA, gradual dose reduction to a minimum dose of one capsule at night (5 mg olanzapine or matching placebo per day) may occur in consultation with the participant’s treating doctor and study psychiatrist. All dosage changes for each participant will be reported. Specific data to determine dose range in this setting is not available. We therefore chose this dose range based on Australian regulatory approval of olanzapine dosages of 5–20 mg to treat other neuropsychiatric conditions, such as schizophrenia and bipolar I disorder [46].

Randomisation to groups (29 participants, or 50% of the total sample of 58 participants per group) will be undertaken by an independent Epworth HealthCare accredited biostatistician employing permuted blocks of random length [47] in line with Consolidated Standards of Reporting Trials (CONSORT) 2010 guidelines [48], employing a procedure such as the ralloc procedure of Stata version 15 or higher. Block sizes will not be disclosed, to facilitate concealment. The randomisation schedule will be supplied by the independent biostatistician to a compounding pharmacist at an on-site compounding pharmacy located at Epworth HealthCare, who will prepare sequentially numbered, sealed opaque envelopes containing the group assignment. Allocation lists in the possession of the independent biostatistician and pharmacy will be stored securely in a password-protected file or locked cabinet.

Following eligibility confirmation, the participant will be enrolled into the trial by study staff and assigned the next available participant number. Randomisation will be requested of the on-site compounding pharmacy by study staff and the pharmacy will dispense treatment in line with that participant’s allocation. Thus, randomisation will be conducted without any influence of allocation awareness by participants, ward staff or investigators. Study product will be compounded as needed in batches. Once randomisation has taken place, a prescription for olanzapine containing the patient’s details including participant number will be signed by the participant’s treating physician and sent to the on-site pharmacy. The pharmacy will then bottle the treatment as appropriate, based on the randomisation schedule. This will be labelled with the participant’s details including study participant number and name. Study product dosage, and any escalation in dosage, will be reflected in the participant’s drug chart. Study treatment will be dispensed in quantities deemed appropriate by study staff, as treatment duration (i.e. PTA duration) is participant-dependent. Study product will be dispensed by the pharmacy and transported to the ward via usual Epworth HealthCare distribution methods or by study staff. Further prescriptions will be signed and sent to the pharmacy as needed.

Upon emerging from PTA as judged by a score of 12/12 on the WPTAS on three consecutive days, olanzapine will be tapered at a rate deemed appropriate by study doctors. Dose reduction or rechallenge may be undertaken in the setting of an adverse event (AE). Intervention may also be discontinued in the following circumstances: (1) following 6 months in PTA, (2) withdrawal of MTDM consent, (3) due to medical considerations or (4) escalation of agitation to an unmanageable level, resulting in physical aggression posing threat of harm to staff or property.

To maximise compliance, study staff will regularly check that treatment has been administered as prescribed by reviewing the participant’s medical chart. Study staff will also complete a treatment log, recording whether dosages have been administered, and dosage amount.

### Rescue medication

In the event that agitation levels escalate to an unmanageable level such that this results in physical aggression posing threat of harm to staff or property, participants may be administered a rescue dose of olanzapine. This decision has been made in the interest of participant retention and to represent such highly agitated patients in the participant pool. Multiple incidents of rescue medication use will prompt consideration of withdrawal from participation by the trial Data Safety Monitoring Committee (DSMC) in consultation with the patient’s treating doctor and study psychiatrist.

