## Abstract

**Background:**

Agitation is common in the early stages of recovery from traumatic brain injury (TBI), when patients are in post-traumatic amnesia (PTA). Agitation is associated with risk of harm to patients and caregivers. Recent guidelines recommend that agitation during PTA is managed using environmental modifications. Agitation is also frequently treated pharmacologically, with the use of atypical antipsychotics such as olanzapine among the most common. This is despite a lack of well-designed studies to support the use of antipsychotics within this context. This study will be a double-blind, placebo-controlled randomised controlled trial. We will examine the efficacy, safety, cost-effectiveness and outcomes associated with the use of olanzapine for reducing agitation in patients in PTA following TBI over and above recommended environmental management.

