## Background

The Australian Institute of Health and Welfare has reported a national traumatic brain injury (TBI) incidence of approximately 107 per 100,000 population per annum [1]. Productivity loss, economic costs and ongoing disability associated with TBI render this health condition a significant global public health concern [1–3]. Traumatic brain injury is frequently followed firstly by a period of coma and secondly by a period of post-traumatic amnesia (PTA). In moderate to severe TBI, PTA represents a period of recovery spanning days to months wherein the patient experiences generalised cognitive disturbance. This cognitive state is characterised by anterograde and retrograde amnesia, confusion, disorientation, attentional dysfunction, low arousal and poor awareness [4–7]. Patients in PTA often exhibit severe neurobehavioural symptoms [8–10]. Perhaps the most challenging of these is agitation, defined as an excess of behaviour involving restlessness, disinhibition and emotional lability [11–13]. When using a standardised measure of agitation, approximately one third of individuals exhibit agitation during the early stages of recovery from TBI [11, 14]. Agitation is problematic for patients, families and healthcare workers. Restlessness may lead to falls, and aggressive behaviour may result in self-harm, destruction of property and violence towards others [15, 16]. Agitation is associated with poorer rehabilitation engagement and longer hospital stays, and agitated patients reportedly exhibit poorer functional outcomes and less frequent return to private homes [8, 14, 17, 18].

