Olanzapine does not show demonstrated effects on cognitive function or recovery following TBI [29] and has a favourable safety profile when used to treat agitation in other conditions [38–41]. It is therefore arguable that olanzapine is suitable for treating agitation in the acute stages following TBI. Olanzapine is commonly prescribed during PTA [26]. There is however a complete lack of quality data regarding the efficacy, harms and other outcomes associated with the use of this drug for the treatment of agitation during the PTA period [19]. We have therefore chosen olanzapine as the active intervention for this placebo-controlled randomised controlled trial. Current evidence for the use of antipsychotics for the management of neurobehavioural symptoms during PTA is limited to case series with no formal comparison condition [19, 32, 42, 43]. Selection of a placebo comparator minimises bias and allows for collection of a higher level of evidence than that presently available. All study participants will receive optimal environmental management for agitation as per guidelines [7] and may receive a ‘rescue dose’ of olanzapine should agitation escalate to unmanageable levels. This permits the evaluation of olanzapine efficacy in conjunction with optimal environmental management over and above environmental management alone. Additionally, optimal environmental management allows for the ethical provision of medical care to this population in line with current guidelines [7] and the reduction of potential risks associated with agitation. The choice of a placebo-controlled design is therefore considered both scientifically rigorous and ethical.

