### Concomitant and post-trial care

All participants will receive environmental management designed to minimise agitation [7] including being located in a secure and quiet ward, avoiding restraint and overstimulation, allowing frequent rest and regulation of visitors to avoid overstimulation. Dedicated, consistent staff will optimise communication, reassurance and orientation. Participants will be permitted to engage in whatever other medical, rehabilitative or pharmacological therapy their medical team deems appropriate. Exceptions to this allowance include the use of medications for agitation (not including trial or rescue medication).

Following completion of the study, participants will continue to receive usual rehabilitation and other services as offered by Epworth HealthCare. Epworth HealthCare will also provide treatment for any drug-related AEs.

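### The rescue-medication trigger expressly covers only threats to staff or property, leaving threats to the participant, other patients or visitors to the clinician's reading

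*Protocol article*

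**What the plan says.** The operative rule is in Rescue medication. When agitation becomes unmanageable and leads to "physical aggression posing threat of harm to staff or property, participants may be administered a rescue dose of olanzapine". Two other places use the same staff-or-property target: the fourth discontinuation ground in Intervention, randomisation and allocation, and the second item of Data Safety Monitoring Committee (DSMC) advice in Harms.

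Elsewhere the article describes the harms more widely. The Background says that "aggressive behaviour may result in self-harm, destruction of property and violence towards others". The Abstract says "Agitation is associated with risk of harm to patients and caregivers". The Background also summarises rescue with no target of harm: participants may have a rescue dose "of olanzapine should agitation escalate to unmanageable levels".

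Concomitant and post-trial care allows other treatment, with one carve-out: "Exceptions to this allowance include the use of medications for agitation (not including trial or rescue medication)". The Discussion gives two reasons for having rescue: to retain highly agitated participants and to protect medical staff. It gives no reason for leaving the participant or other non-staff persons out of the trigger.

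**The concern.** The rule that ward staff would apply is narrower than the harms the protocol itself attributes to aggression, and narrower than its own summary of rescue. Consider a participant whose unmanageable physical aggression endangers only himself, a fellow patient or a relative. The clinician must decide whether to follow the trigger as written or the looser Background sentence.

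Two things are at stake. The first is safety: a cautious clinician may withhold a dose that the protocol probably intends to allow, in people who are in post-traumatic amnesia and cannot consent for themselves. The second is consistency: the Discussion plans to compare rescue doses between groups, and that count is harder to interpret if clinicians apply different thresholds.

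**Working it through.** No formula applies, because the point does not depend on alpha, power, effect size, standard deviation or attrition. The check sets the texts side by side.

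**Step 1. Harms named in the Background against the trigger in Rescue medication.**

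| Result of aggression (Background) | Expressly covered by the trigger? |
|---|---|
| Destruction of property | Yes |
| Violence towards others | In part: only where the others are staff |
| Self-harm | No |

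That is 1 of 3 covered fully, 1 of 3 in part and 1 of 3 not at all. This counts wording and does not measure risk.

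**Step 2. Does any other text widen the trigger?** Rescue or unmanageable agitation is mentioned in the Background, in Intervention, randomisation and allocation, in Rescue medication, in the treatment-period section, in Concomitant and post-trial care, in Harms and in the Discussion. None of these adds the participant or other non-staff persons as a target of harm. The Background sentence names no target at all, so it can be read to include them, but it is a summary and not the operative rule.

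**Step 3. Do other provisions give the same acute option?**
- Other agitation drugs are excluded by Concomitant and post-trial care. Drugs still being weaned at entry (Screening) are a transitional exception.
- Dose escalation is possible only every 3 to 4 days. In the placebo arm it adds only placebo capsules, so once any weaning is complete, rescue is the only on-protocol active drug for agitation in that arm.
- Discontinuation for medical considerations and the adverse-event routes (the treatment-period section and Harms) lead to stopping, dose reduction, rechallenge or withdrawal. They do not state that an acute dose may be given. The adverse-event questionnaire is weekly, and its listed symptoms do not include self-injury or aggression.

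**Step 4. Effect on stated figures.** None. The effect size of 0.80, 26 per group, 10% attrition and 29 per group all stand. The article gives no frequency for the episodes in question, so no effect on the agitation-score comparison, rescue counts or attrition can be derived.

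**The case against.** The strongest objection concerns a stronger reading that a reader might infer: that a participant who threatens only himself, another patient or a visitor cannot receive rescue on protocol. The documents do not support this. The rule is permissive, does not say that rescue is limited to the case described, and prohibits nothing. The Background describes rescue for unmanageable agitation without naming a target, and the concomitant-care rule exempts rescue medication without attaching a condition. This objection stands in full.

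The practical gap is probably small. Participants are cared for by dedicated staff, "being located in a secure and quiet ward" being part of environmental management. Staff who step in will often be under threat themselves, and the trigger is then met. Participant safety has other routes, through discontinuation for medical considerations and the adverse-event provisions. Withdrawal need not lose outcome data, since Retention seeks continued collection for the intention-to-treat analysis. These points stand, and they keep the severity low.

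It can also be said that staff-or-property is a deliberate threshold, used three times, and that a narrow trigger is sensible when the rescue drug is the trial drug. This stands only in part. The Discussion explains why staff are protected and accepts that rescue blurs the two arms, but it does not argue for excluding threats to the participant or other patients.

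Finally, this is a condensed article, and the full protocol is not shown. That excuses details such as rescue dose, route or maximum. It does not excuse the target of harm, which the article does state, and states narrowly.

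**Conclusion.** The point holds as a minor defect in a stated safety rule. The trigger does not expressly cover threats to the participant, other patients or visitors, although the article names harm to patients, self-harm and violence towards others among the risks. The likely consequence is uneven use of rescue, with some participants possibly not given it on protocol.

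Nothing supports going further. The text contains no bar on rescue in these cases. With no episode frequency given, no bias in the primary comparison and no extra attrition can be claimed.

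The conclusion rests on two assumptions: that ward practice follows the Rescue medication section and not the Background summary, and that the full protocol uses the same wording. If the full protocol already names the participant and other persons, only the article needs correcting.

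**What to change.** In Rescue medication only, change the target of the threat from staff or property to: *the participant, other persons (including staff) or property*. Keep the condition that unmanageable agitation has resulted in physical aggression. Rescue then stays narrower than the Background summary, and restlessness that might lead to a fall remains outside it.

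Leave the discontinuation ground and the DSMC withdrawal item unchanged, because widening them would enlarge the grounds for taking people off treatment. The rescue and withdrawal thresholds will then differ. Add a sentence saying that this is intended, so that it is not taken for an inconsistency.

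The cost is one phrase and one explanatory sentence, with no new data, staff or analysis. There are two downsides. The placebo arm may receive a few more olanzapine doses, slightly diluting the contrast; the Discussion already acknowledges this drawback and plans to compare rescue doses by group. There may also be a few more participants with repeated rescue, and "Multiple incidents of rescue medication use will prompt consideration of withdrawal from participation".

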The primary aim of this trial is to evaluate the efficacy of the atypical antipsychotic olanzapine in reducing agitation in patients in PTA following TBI over and above recommended environmental management. We hypothesise that patients who are administered olanzapine will show lower levels of agitation during PTA than those randomised to a placebo control group receiving optimal environmental management. The secondary aims of this research are to determine (1) the safety of olanzapine administration in PTA patients, whether olanzapine treatment: (2) reduces the number of clinically agitated days during PTA, (3) alters level of agitation at hospital discharge, (4) alters level of cognition in PTA, (5) alters PTA duration, (6) alters cognitive performance following PTA emergence, (7) alters length of inpatient hospital stay and (8) alters functional independence at discharge and 3-month follow-up. Finally, this research aims to evaluate the cost-effectiveness of olanzapine administration in PTA patients.

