#### Treatment—day 0 until emergence from PTA (or 6 months maximum)

The treatment period will last from day of completion of baseline assessments until the patient is deemed to have emerged from PTA or until 6 months have elapsed. Emergence from PTA is defined as the first of three consecutive days on which a score of 12/12 on the WPTAS is achieved. Participants will be administered their randomised dose. They will also receive optimal environmental management as per guidelines [7]. WPTAS and ABS scores will be recorded by nursing staff or the patient’s clinical neuropsychologist. Need for dosage escalation and rescue medication use will be monitored by study staff. To describe concomitant care and inform health-economic evaluation, the number of patients on the ward, therapy hours and number of sessions and medication use including name and dose regimen will be recorded from the participant’s medical file.

AE monitoring will occur weekly. Clinically significant changes in these parameters will be recorded as AEs and a decision made by the treating doctor in consultation with a psychiatrist and the DSMC as to whether serious AEs necessitate withdrawal from the study.

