### Outcomes and measures

#### Primary outcome

To assess the efficacy of the atypical antipsychotic olanzapine in reducing agitation in patients in PTA following TBI over and above recommended environmental management, we will examine the difference between active and placebo groups’ mean daily score on the ABS during PTA. This outcome will include all daily ABS assessments throughout the treatment period. The ABS is a widely used measure of agitated behaviour in TBI [56–58]. Completion involves the observer rating the presence of 14 agitated behaviours based on the past 8-h period. Internal consistency is high, and construct validity and inter-rater reliability have been established [57–60]. Nurses and clinical neuropsychologists who complete the ABS at Epworth HealthCare are trained in its use.

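### Rescue is the test drug in both arms: the agitated-day count can score a rescue day as non-agitated, and the Background names a contrast without rescue that the trial does not make

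*Protocol article*

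**What the plan says.** **Rescue.** Under Rescue medication, when agitation becomes unmanageable and leads to threatening physical aggression, "participants may be administered a rescue dose of olanzapine". Nothing restricts this by arm, and the Background says it applies to all participants. Concomitant and post-trial care exempts rescue from the ban on other agitation drugs. Repeated use has consequences: "Multiple incidents of rescue medication use will prompt consideration of withdrawal from participation". The grounds for stopping treatment under Intervention, randomisation and allocation include "4) escalation of agitation to an unmanageable level, resulting in physical aggression".

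**Outcomes.** The primary outcome is the mean daily ABS score during post-traumatic amnesia: "This outcome will include all daily ABS assessments throughout the treatment period". The scale involves "rating the presence of 14 agitated behaviours based on the past 8-h period". Secondary outcome 2 is the number of days with ABS above 21. Rescue does not enter that definition. Statistical methods analyses patients as randomised.

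**Stated contrast.** The Background mentions rescue olanzapine and, in the next sentence, says: "This permits the evaluation of olanzapine efficacy in conjunction with optimal environmental management over and above environmental management alone".

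**Disclosure and recording.** The Discussion concedes that olanzapine rescue blurs the division between the arms, gives reasons for it, and promises a between-group comparison of rescue doses. In the treatment-period section, "Need for dosage escalation and rescue medication use will be monitored by study staff", and medication names and dose regimens are taken from the medical file.

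**The concern.** Rescue is triggered by the behaviour that the trial measures, and it is given with the drug under test. Two consequences follow.

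1. **Agitated-day count.** A day bad enough to need rescue is among the worst that a patient can have. It is counted as agitated only if the ABS rating exceeds 21. The rating can be 21 or below because the episode fell outside the rated 8 hours, or because the rescue dose calmed the patient for much of them. If scheduled olanzapine works, rescue should be commoner on placebo. More bad days would then be lost from the placebo count, and the difference between arms would shrink.

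2. **Named contrast.** Because placebo patients may receive olanzapine, the control strategy is not environmental management on its own. A null result could be reported as showing no benefit over environmental management without the drug, a comparison that the trial does not make.

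**Working it through.** **Plan's own figure.** The planned difference is 0.80 × 4.1 = 3.28 ABS points (Sample size). A two-sample t test with standardised difference 0.80, power 0.80 and two-sided alpha 0.05 needs 25.5 per group, rounded up to 26. Then 26 / 0.90 = 28.9, rounded up to 29. Both stated figures reproduce. Power at 26 per group is 0.807.

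**Assumed inputs.** The protocol gives no rescue rate, so all of these are assumptions:
- Share of placebo patients rescued: 20% to 60%; on olanzapine, half that.
- Rescue days per rescued patient: 1 to 3. The stopping and withdrawal provisions make sustained rescue unlikely.
- Share of rescue days scored 21 or below: 0, one half or 1.
- For the primary only: ABS falls by 4 to 8 points, on the rescue day alone.

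**Agitated-day count.** Days missed per patient = share rescued × rescue days × share scored 21 or below. If every rescue day is scored 21 or below:
- Placebo: 0.2 × 1 = 0.2 to 0.6 × 3 = 1.8.
- Olanzapine: 0.1 × 1 = 0.1 to 0.3 × 3 = 0.9.

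| Share of rescue days scored 21 or below | Net days lost from the difference |
|---|---|
| All | 0.1 to 0.9 |
| Half | 0.05 to 0.45 |
| None | 0 |

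If rescue is equally common in both arms, the net loss is also 0.

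**Primary, read against environmental management without rescue.** Net understatement = 0.5 × share rescued on placebo × (rescue days / treatment days) × ABS fall. The factor 0.5 is the placebo rate minus the half rate on olanzapine. For 28 treatment days:
- Low: 0.5 × 0.2 × (1/28) × 4 = 0.014 points.
- High: 0.5 × 0.6 × (3/28) × 8 = 0.257 points. The difference becomes 3.28 − 0.257 = 3.02, or 0.737 SD.

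| Treatment days | Understatement (points) | Share of 3.28 | Equivalent power at 26 per group |
|---|---|---|---|
| 14 | 0.029 to 0.514 | 0.9% to 15.7% | 0.80 to 0.67 |
| 28 | 0.014 to 0.257 | 0.4% to 7.8% | 0.80 to 0.74 |
| 56 | 0.007 to 0.129 | 0.2% to 3.9% | down to 0.78 at the upper end |

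These figures take 3.28 as the difference that would be seen without rescue and use the t test of the sample-size section, not the planned mixed model. With equal rescue in both arms the understatement is zero.

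**Contrast, by reading.** Rescue is open to both arms, all daily ABS scores count, and patients are analysed as randomised. The Retention section also seeks consent to continue outcome collection after withdrawal. Together these define a comparison of two treatment policies: scheduled olanzapine, or placebo, each with environmental management and olanzapine rescue as needed. The Background sentence omits rescue from the comparator, and the Discussion's concession does not correct it.

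**The case against.** **Much is disclosed.** The Background mentions rescue immediately before the criticised sentence, and the Discussion names the limitation, justifies it and compares rescue doses. That stands, and it is a reason to rate the point low. But comparing doses does not change how a rescue day enters the count, and the comparator is still described wrongly.

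**The count is clear and partly not a rescue problem.** ABS above 21 is also the threshold for eligibility and dose escalation. A rating covering 8 hours can miss an aggressive episode whether or not rescue is given. An episode inside the rated window is rated. Leaving a discretionary staff decision out of the definition is defensible. This stands as a reason to keep the existing count, but not as a reason to report it alone.

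**Such detail belongs in the statistical analysis plan.** A supportive count could sit there, and its absence from the article would be no finding. The outcome definition and the stated contrast, however, are fixed in the article itself.

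**Stronger readings that the documents do not support.**
- A reader might infer that rescue biases the primary analysis or leaves the trial underpowered. The analysis is unbiased for the policies it compares. A loss of 10% to 30% of the planned effect would lower power to 0.72 to 0.51, but nothing in the protocol leads to a loss of that size.
- A reader might also fault the hypothesis, which expects less agitation "than those randomised to a placebo control group receiving optimal environmental management", and the cost comparison, because both name the control without rescue. That is ordinary shorthand for the randomised arms. Medication use is costed from the medical record, so rescue can be captured.

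**Conclusion.** The point holds in two limited parts, and its severity is minor. First, secondary outcome 2 can score a day of physical aggression and rescue as non-agitated. If rescue is commoner on placebo, the difference between arms shrinks. The protocol does not allow the amount to be computed. The 0 to 0.9 days shown rest entirely on assumed rescue rates, and the true figure may be small. Second, the Background misnames the contrast, and this holds whenever rescue is available, whatever its rate. The primary analysis needs no change. What needs limiting is the conclusion that a null result may support.

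**What to change.** 1. Keep the ABS-only agitated-day count as secondary outcome 2. Report beside it a count in which any day with a rescue dose is agitated, and fix this before unblinding. The cost is one extra count. It needs the date of each rescue dose. The article does not list that item, but rescue use is monitored and medication is taken from the medical file. The registered outcome is not redefined, which matters because the Trial status section reports 5 patients recruited. The downside is that the added count partly reflects a discretionary staff decision, although ward staff are blinded.

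2. Reword the contrast in the Background as scheduled olanzapine versus placebo, both with environmental management and olanzapine rescue as needed. Add that a null result will not be read as no benefit over environmental management without rescue. The cost is two sentences.

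Replacing rescue-day ABS scores with pre-rescue values in the primary is not recommended here. It ignores carry-over to later days, does not estimate the effect against environmental management without rescue, and is a debatable choice for the statistical analysis plan.
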